#### SCED Procedure

We created a working version based on the Risk of Bias in N-of-1 Trials (RoBiNT) scale, a critical evaluation tool to evaluate the methodological quality of intervention studies using single-case methodology (Tate et al., 2013). We outlined the procedure for routine clinical care and research projects that could use the infrastructure of the single-case clinic in the future. For routine clinical care, we plan to use a replicated ABCDE design in which EMA data is collected after the initial appointment (phase A: baseline), during up to five diagnostic sessions (phase B: diagnostic), and during the first treatment sessions (phase C: intervention). Whenever psychotherapists alter their treatment focus or change their therapeutic strategies, they can initiate a new intervention phase (phase C’, phase C’’, etc.). This allows them to directly continuously evaluate their respective therapeutic approach. Furthermore, ESM data will be collected after treatment has ended (phase D: posttreatment) and at 6-months follow-up (phase E: follow-up). Further details can be found in Table 1.

**Table 1 Tab1:** Working version for the implementation of the single-case clinic based on the RoBiNT Scale (Study 2)

Item	RoBINT Scale	Suggestions for the implementation into routine clinical care	Possibilities for future research projects
*Internal validity subscale*			
1	Design	Replicated ABCDE Design A: baseline phase B: diagnostic phase C: intervention phase (C’, C’’, etc.) D: posttreatment phase E: follow-up phase	Replicated *randomized* designs Multiple baseline designs (concurrent and non-concurrent)
2	Randomization	No randomization due to practice-oriented focus	Randomization of treatment start per patient; randomization of treatment components (and their order)
3	Sampling behavior (all phases)	Baseline, diagnostic, posttreatment, and follow-up phase: 14 surveys per phase Intervention phase: open end	At least 5 data points per phase; patients with less than 3 data points per phase should be excluded from any statistical analysis
4	Blinding patient/psychotherapist	Blinding not possible and unethical	Blinding options are restricted in psychological treatments; in the case that interventions are compared against each other, neither patients, psychotherapists, nor supervisors should be informed about the research hypothesis

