#### ESM Protocol

We followed systematic guidelines to consider different arguments when making methodological decisions (Janssens et al., 2018). A decision matrix was created that organizes different arguments along methodological questions (Supplemental Material, S3 Decision matrix for methodological questions, https://osf.io/54ewu). Arguments include the nature of the variable of interest, reliability and feasibility issues, as well as statistical requirements. Open methodological questions include study duration, measurement frequency, number of items, sampling scheme, instruction of items, and delay allowed to respond. The matrix was filled with typical practices or recommendations for ESM studies found in the literature (Eisele et al., 2020; Janssens et al., 2018; Wrzus & Neubauer, 2023). Based on the matrix, the research team formulated methodical suggestions for the SCED infrastructure regarding each methodological question. We decided to omit the issue of statistical requirements. Instead, future studies using the SCED infrastructure should discuss statistical requirements for the respective research question and analysis in a separate pre-registration in the Open Science Framework (https://osf.io/yex48/).

We propose to collect ESM data on 14 consecutive days during each SCED phase. We decided to not limit the study duration during the intervention phase with the aim to gather information about the extent that the daily surveys are used during treatment. Alternatively, a second (or more) 14-day assessment periods could be prompted during treatment (phase C’ or C’’ etc.). We suggest to collect one signal-contingent survey per day with the option of additional event-contingent surveys whenever the patient feels something important had happened. Each event-contingent survey will trigger a measurement burst with additional five surveys, randomly presented within the following hour. This measurement burst enables to monitor momentary mood on a microlevel. We decided to apply a semi-random sampling scheme with random beeps during an individualized time in the evening (e.g., 18-22 h). As delay allowed to respond, we suggest 60 min for the signal-contingent survey with a reminder after 30 min. For the event-contingent survey, we decided to close the survey after 30 min.

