### Study 5: Piloting the Implementation of the SCED Infrastructure

The study aims (1) to determine how users accept, perceive, adopt, and integrate the SCED infrastructure into routine clinical care and (2) to use results to initiate strategies for further improvement. For that reason, the SCED infrastructure will be offered in routine clinical care to generate first evidence regarding perceptual and behavioral implementation domains. We intend to offer all new admissions to our clinic to use the SCED infrastructure for a 1-year period. Both patients (irrespective of their clinical diagnosis except for acute suicidal tendencies and psychotic symptoms) and psychotherapists will be invited to participate in the implementation study. We expect to have approximately 250 new admissions in a 1-year period. On average, during the last five years we had 295 new admissions per year, but due to the change of the system we expect a slight decrease. In 2021 and 2022, we had 77 active psychotherapists and 72 respectively. The number of patients and psychotherapists who decide to use the infrastructure will be used to estimate the adoption rate as one implementation outcome (see Section “Implementation Outcome Measures” and Table 3 for more information).

**Table 3 Tab3:** Implementation Outcome Domains and Measures (Study 5)

Domain	Definition	Concrete Operationalization	Measure	Criteria

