Penetration	Penetration refers to the integration of a practice within a setting	Number of patients and psychotherapists who actually use the SCED infrastructure (e.g., in terms of responding to the ESM surveys; retrieving and discussing the dashboard during treatment or supervision)	(5) ESM data (including signal- and event-contingent surveys of completed ESM surveys (i.e., the last question has been answered)) is used to derive an estimate for the penetration: • Exploration of arithmetic values (e.g., median, range, mean standard deviation) for the number of completed ESM surveys for each SCED phase, especially for the open-ended intervention phase • RoBiNT scale requires each phase to consist of at least five, but not less than three data points for the analysis of SCED data (Tate et al., 2013). We will evaluate each phase separately, with ≥ 5 data points as an acceptable criterion. For each phase, we divide the number of patients who fulfill the acceptable (≥ 5 data points) criterion by the number of participating patients (6) Indication how often patients and psychotherapists retrieved the dashboards either to prepare for treatment or discuss the dashboard during treatment on a 5-point Likert scale (1 = never to 5 = every session) after each SCED phase. Psychotherapists will also be asked to indicate how often they discussed the dashboard with their supervisors • *‘How often did you retrieve the dashboard (e.g., to prepare for treatment or discuss the dashboard during treatment)?’* • *‘How often did you discuss the dashboard together with your supervisor?’*	(5) A rate ≥ 75 is considered substantial use (6) Mean scores of > 3.5/5 on each item are considered substantial use
Implementation costs	All costs needed for an implementation effort	All monetary resources needed for the implementation of the SCED infrastructure. These costs could either be anticipated (e.g., for the m-path software) or unexpected (i.e., they only become clear in the course of implementation)	Implementation costs are also difficult to calculate because they vary substantially in the different settings (7) A list of the costs we have incurred (e.g., required working time of an employee to coordinate the single-case clinic)	

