Results of the initial implementation study will be a first indicator for the expected sustainability of the SCED infrastructure in our clinic. In case, results do not meet our predefined criteria for a successful implementation, the research team will develop a proposal for another implementation strategy plan (Kirchner et al., 2020b; Powell et al., 2015) to maintain and further improve the uptake of the SCED infrastructure. Other implementation strategies could comprise the provision of interactive assistance or the training of stakeholders. Again, the implementation plan will be optimized and finalized together with different stakeholders. In either case, we plan to replicate the pilot implementation study for another year, with the goal to either test whether implementation outcomes substantially improve compared to the first implementation round or to evaluate its sustainability.

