#### Implementation Outcome Measures

Perceptual and behavioral outcome measures were selected in accordance with a generally recognized taxonomy for outcome domains in implementation research (see Table 3; Proctor et al., 2011). For our study purposes, we considered the outcome domains acceptability, appropriateness, adoption, and penetration. In addition, we plan to report on compliance and retention rates as indicators inherently linked to ESM studies. Criteria for a successful implementation were chosen according to previous research (Schleider et al., 2020). Criteria for compliance and retention rates were formulated based on systematic reviews (Rintala et al., 2019; Vachon et al., 2019; Wrzus & Neubauer, 2023). We decided to omit the domains of feasibility, fidelity, and sustainability as these issues are addressed in the other phases of the agile research framework. For example, feasibility will be ameliorated and tested in phase 3, while sustainability will be addressed in phase 5. Likewise, it is difficult to include fidelity in an agile research framework as methodological decisions can change based on outcomes from previous phases. We have chosen behavioral measures whenever possible. Given the general lack of unified implementation measures with mostly unknown psychometric quality, questionnaires to assess perceptual outcomes were selected based on a recent systematic review evaluating the psychometric properties of implementation measures (Mettert et al., 2020). Perceptual implementation outcome measures will be collected from both patients and psychotherapists when they decide whether they want to use the SCED infrastructure prior to treatment. Perceptional implementation outcomes will also be administered after each SCED phase to record their development over time. In the intervention phase, implementation measures will be administered 6 weeks after the intervention started. If the post-treatment and follow-up phases are not yet available for all patients at the time of data analysis, patients will be invited to take part in another 14 ESM assessment days and to provide concluding information on perceptual implementation outcome measures.

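### Survey use in the open-ended intervention phase is summarised as a raw count, so the figure shifts with the data-cut date if patients are still in that phase at analysis

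*Protocol article*

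**What the plan says.** All references are to the protocol article.

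- **The statistic.** Study 5, Table 3, Penetration, measure (5), first bullet: exploratory summary values (median, range, mean, SD) "for the number of completed ESM surveys for each SCED phase, especially for the open-ended intervention phase". Signal-contingent and event-contingent surveys both count. The second bullet takes the share of participating patients with at least five data points in each phase; the criterion of 75 is a rate and so can only belong to that bullet.
- **The phase.** Table 1 has "Intervention phase: open end", and the ESM Protocol section says "We decided to not limit the study duration during the intervention phase". The purpose stated there is to see how much patients use the daily surveys while they are being treated. New intervention phases (C', C'') may be started when the treatment focus changes.
- **Entry and length.** Study 5: "We intend to offer all new admissions to our clinic to use the SCED infrastructure for a 1-year period", and "We expect to have approximately 250 new admissions in a 1-year period". Under Setting, treatment usually has 24 sessions and can be extended to 80.
- **Unfinished patients.** Implementation Outcome Measures: "If the post-treatment and follow-up phases are not yet available for all patients at the time of data analysis", patients are invited to another 14 days of ESM assessment. That stands in for the later phases and does not alter the intervention-phase count. The same section places the perceptual measures in the intervention phase at 6 weeks, a fixed point not applied to the survey count.
- **Second year.** Study 5 is to be repeated, either to evaluate sustainability or to "test whether implementation outcomes substantially improve compared to the first implementation round".

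**The concern.** The intervention phase was left open to learn how much daily surveys are used in treatment, and the raw count is the figure Table 3 names for the amount of use. A count over an unlimited phase can be read only if patients were observed for comparable times. With entry spread over 12 months, a patient admitted early may contribute the whole phase and one admitted late only a few weeks. The count is then partly a record of admission date.

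At stake are two things: a description of use that is too low, and a year-to-year comparison that can shift because observation time differs although behaviour does not. The article leaves the timing of the analysis open. That is no fault in a condensed report, but it means the size of the effect can only be given as a range.

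**Working it through.** The article gives no expected count, so there is no figure of its own to reproduce. The check asks how far a raw count moves with the cut date when behaviour is held fixed.

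**Inputs from the article:** entry over 1 year; 24 or 80 sessions; one signal-contingent survey per day; completion of 0.70 (lower end of the range Table 3 calls satisfactory compliance).

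**Assumptions:** entry e uniform over 365 days; weekly sessions, so phase length D = 168 days (24 sessions) or 560 days (80 sessions); lead time L from admission to the intervention phase of 28 or 49 days; event-contingent surveys ignored; cut T counted from first admission.

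**Formula.** Available time is A = T − e − L. Among patients who have reached the phase, mean count = 0.70 × mean of min(A, D).

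**24 sessions, 12-month cut.** A is uniform from 0 to 365 − L, so the mean observed time is [D²/2 + D(365 − L − D)] / (365 − L).
- L = 28: (14,112 + 168 × 169)/337 = 126.1 days; × 0.70 = 88.
- L = 49: (14,112 + 168 × 148)/316 = 123.3 days; × 0.70 = 86.
- Full phase: 168 × 0.70 = 118. The mean is 25% to 27% low.

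**24 sessions, later cuts.** Everyone has entered the phase, with shortest available time Amin = T − 365 − L. The mean shortfall is (168 − Amin)²/(2 × 365).
- 15 months (T = 456): 105²/730 = 15.1 days and 126²/730 = 21.7 days, so 9% and 13% low.
- 18 months (T = 547): 14²/730 = 0.3 days and 35²/730 = 1.7 days, so 0.2% and 1.0% low.

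**80 sessions, 12-month cut.** Nobody has finished. Mean time is (365 − L)/2 = 168.5 or 158 days, giving 118 or 111 against 560 × 0.70 = 392.

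Simulation agrees with these results. It also covers patients who stop answering after an exponential time (24 sessions, L = 49):

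| Scenario | Full-phase mean | 12 months | 15 months | 18 months |
|---|---|---|---|---|
| 24 sessions, steady use | 118 | 86–88 (25–27% low) | 102–107 (9–13%) | 116–117 (1% or less) |
| Stop after mean 84 days | 50.8 | 41.6 (18%) | 47.2 (7%) | 50.7 (under 1%) |
| Stop after mean 42 days | 28.9 | 25.3 (12%) | 27.8 (3%) | 28.8 (under 1%) |
| Stop after mean 21 days | 14.7 | 13.7 (7%) | 14.6 (1%) | 14.7 (0%) |
| 80 sessions, steady use | 392 | 111–118 (70–72%) | 157–172 (56–60%) | 221–236 (40–44%) |

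**Median.** With 24 sessions and steady use it hardly moves at 12 months (111 to 118 against 118). With early stopping it is 7%, 12% and 22% low (9.5 against 10.2, 17.9 against 20.4, 31.7 against 40.7).

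**Share unfinished with 24 sessions:** 54% to 59% at 12 months (including 28/365 = 8% to 49/365 = 13% not yet in the phase), 29% to 35% at 15 months, 4% to 10% at 18 months.

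**Success criterion.** With steady use, the share with at least five data points in the intervention phase is 85% to 90% of all enrolled at 12 months and 100% from 15 months, against a criterion of 75.

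**Behaviour of the alternatives.**
- Count in the first 42 days, among patients with all 42 available: 0.70 × 42 = 29 at any cut with steady use. With stopping after a mean of 42 days it is 0.70 × 42 × (1 − e⁻¹) = 18.6 at any cut.
- Surveys per available day: 0.70 at any cut with steady use. With the same early stopping it is 25.3/123.3 = 0.21 at 12 months against 28.9/168 = 0.17 over the full phase, so here the rate moves upwards.

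**The case against.** The case against has real weight.

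- **Nothing is decided on this bullet.** It is exploratory, its list of summaries is open, and it has no threshold. Corrective action in Study 5 depends on the predefined criteria, and this count is not one of them. This stands.
- **A time-adjusted measure already exists.** Measure (8) divides completed by theoretically possible signal-contingent surveys. This stands in part: it leaves out event-contingent surveys and does not say what is possible in a phase without an end.
- **An early cut is not stated.** A reader might infer that many patients will still be in the intervention phase at analysis. The article does not say so. Its remark on unfinished patients is conditional and concerns the post-treatment and follow-up phases; someone awaiting the 6-month follow-up may have finished the intervention phase long before. An early cut is plausible because year-1 results steer the next step, but it is an inference.
- **The effect fades.** Under another model (40-week treatment, 75% of days answered, 7-week lead, exponential stopping) a median of 68 falls to about 47 at week 52 when half stop by 13 weeks. By week 78 the deficit has gone for median stopping times of 8 and 13 weeks; about 11% to 12% remains at 26 weeks.
- **A replicated year may be cut alike.** Similar truncation in both years would largely cancel. The artefact needs unequal observation time, which the article neither plans nor rules out.

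**Conclusion.** The point holds as a weakness in a descriptive measure. A raw count in a phase without an end, with entry staggered over a year, depends on time available. With 24 weekly sessions the mean is about 7% to 27% low at a 12-month cut and about 1% or less low at 18 months; longer treatment makes it worse. These sizes rest on assumed weekly spacing, lead time, completion and stopping patterns. The dependence on the cut rests only on the design as described, provided some patients are unfinished.

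Two stronger readings are not supported. One is that the pilot could be wrongly judged a success or failure: the rate that carries the criterion is barely touched. The other is that the comparison between years is bound to be distorted: that follows only if observation time differs between the rounds.

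**What to change.** In Table 3, measure (5), for the intervention phase including C' and C'':

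1. Keep the raw count, and add completed surveys per available patient-week or the count within a common window, such as the first 6 weeks already used for other measures.
2. State the data-cut date and the number of patients still in the phase.
3. Use the time-adjusted figure for any comparison of year 1 with year 2. The common window is the safer of the two, because the patient-week rate is free of the cut date only if answering is steady over time.

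A Kaplan-Meier curve of time to the last survey, censoring those still responding, is an optional supplement. It should not replace the count: it needs an arbitrary inactivity rule, does not deal with restarted phases, and drops event-contingent surveys if based on signal-contingent ones. Raw counts remain suitable for the phases fixed at 14 surveys.

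The cost is a wording change and a little analysis on time stamps already recorded. A fixed window omits later use and patients without the full window: at a 12-month cut, 42 days are complete for (365 − 28 − 42)/365 = 81% or (365 − 49 − 42)/365 = 75% of those admitted, under the two lead times above.

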#### Implementation Outcome Measures

Perceptual and behavioral outcome measures were selected in accordance with a generally recognized taxonomy for outcome domains in implementation research (see Table 3; Proctor et al., 2011). For our study purposes, we considered the outcome domains acceptability, appropriateness, adoption, and penetration. In addition, we plan to report on compliance and retention rates as indicators inherently linked to ESM studies. Criteria for a successful implementation were chosen according to previous research (Schleider et al., 2020). Criteria for compliance and retention rates were formulated based on systematic reviews (Rintala et al., 2019; Vachon et al., 2019; Wrzus & Neubauer, 2023). We decided to omit the domains of feasibility, fidelity, and sustainability as these issues are addressed in the other phases of the agile research framework. For example, feasibility will be ameliorated and tested in phase 3, while sustainability will be addressed in phase 5. Likewise, it is difficult to include fidelity in an agile research framework as methodological decisions can change based on outcomes from previous phases. We have chosen behavioral measures whenever possible. Given the general lack of unified implementation measures with mostly unknown psychometric quality, questionnaires to assess perceptual outcomes were selected based on a recent systematic review evaluating the psychometric properties of implementation measures (Mettert et al., 2020). Perceptual implementation outcome measures will be collected from both patients and psychotherapists when they decide whether they want to use the SCED infrastructure prior to treatment. Perceptional implementation outcomes will also be administered after each SCED phase to record their development over time. In the intervention phase, implementation measures will be administered 6 weeks after the intervention started. If the post-treatment and follow-up phases are not yet available for all patients at the time of data analysis, patients will be invited to take part in another 14 ESM assessment days and to provide concluding information on perceptual implementation outcome measures.

### Study 6: Implementation of the SCED Infrastructure

The aim of the study during the *implementation phase* is to evaluate the SCED infrastructure compared to routine diagnostic procedures prior implementation. A quasi-experimental single case AB-design with the outpatient clinic as entity will be conducted. The design has the advantages that it reduces confounders (e.g., secular trends, seasonality) and allows to measure long-term effects (Bernal et al., 2017). We will use a continuous sequence of outcome data taken repeatedly over time from the outpatient clinic prior implementation and compare it to outcome data post implementation. This time series is used to estimate an interrupted time series regression. An underlying trend is established, which is ‘interrupted’ by the implementation of the SCED infrastructure at a known point in time (Bernal et al., 2017). Therefore, pre- and post-implementation need to be clearly distinguished (Miller et al., 2020). A graphical example of an interrupted time series is presented as Supplemental Material (S1 Design illustrations, https://osf.io/dkytg).

In our case, data are considered for the pre-implementation phase up to the start of Study 5 and for the post-implementation phase after the completion of Study 5, when the SCED infrastructure is introduced for everyone into routine clinical care. Two items assessing satisfaction and burden of the diagnostic procedure (that includes the ESM assessments after the implementation of the SCED infrastructure) will be used to evaluate the new diagnostic procedure. In addition, we will take an exploratory look at clinical effectiveness using the Symptom Checklist – 90 (Derogatis & Unger, 2010; Franke, 2014). We expect a slight level and slope change regarding clinical effectiveness because research has shown that self-monitoring already effects outcomes positively leading to level change (Bartels et al., 2019; Guo & Albright, 2018; McBain et al., 2015; Simons et al., 2015). In addition, the continuous feedback might reduce treatment failure and improve the positive effects of psychotherapy for example through enhanced tailoring (Lambert & Harmon, 2018; Lutz et al., 2019), leading to a temporary slope change resulting in a level change.

